### Statistical analyses of the primary endpoint

The analysis of the primary composite endpoint at 1 year after treatment will be performed using logistic regression analysis, adjusted for sex, and LVEF category, as these were stratification variables for randomization. Missing echocardiographic data will be imputed using multiple imputation with fully conditional specification. The amount of imputations will be set to the percentage of incomplete records. Predictive mean matching will be used to draw imputations, retaining the original distributional characteristics. A complete case analysis will be used as a sensitivity analysis.

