### Patient population

The trial is performed in adult patients with a permanent pacing indication because of AV block (class I or IIa according to the 2021 ESC guidelines^19^) with an expected ventricular pacing percentage of ≥ 20% and a left ventricular ejection fraction (LVEF) ≥ 40%. Inclusion and exclusion criteria are provided in *Table 1*.

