### Randomization, blinding, and treatment allocation

Patients are randomized in a 1:1 ratio via an interactive response technology system by block randomization. Random permuted block sizes will be used to prevent prediction of treatment allocation before randomization. Randomization will be stratified by sex and percentage of LVEF (i.e. LVEF <50% and LVEF ≥50%) to ensure an even distribution of these characteristics between the two treatment groups. Given the nature of the treatment arms, the participating patients and treatment team are not blinded. Adjudication of the endpoints is performed by a blinded committee.

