## Endpoints

### Primary endpoint

The primary endpoint is the composite of all-cause mortality, hospitalization for heart failure, and a more than 10%-point decrease in LVEF leading to an LVEF below 50%, which as a binary combined endpoint will be determined at 1-year follow-up.

Heart failure hospitalization is defined as:

Hospitalization or unplanned hospital visits for heart failure requiring intravenous diuretics and/or (adjustment) of other medical heart failure therapy.Or hospitalization for upgrade to cardiac resynchronization therapy (CRT) (biventricular pacing) for progression of heart failure with worsening NYHA class and/or (increased) need for diuretic therapy or other medical heart failure therapy.Or hospitalization for upgrade to CRT for developing a class I indication for CRT.Or hospitalization or unplanned hospital visit for heart failure triggered by an episode of atrial fibrillation with uncontrolled heart rate requiring intravenous diuretics or adjustment of rate control therapy.

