### Adjudication of endpoints

All clinical endpoints as described above are adjudicated by an independent, blinded endpoint adjudication committee (EAC). The EAC consists of three experienced cardiologists. Two of them adjudicate all clinical endpoints. In case of disagreement, after discussion with the third committee member, they decide on the adjudication of the endpoint. All endpoints are adjudicated using standardized definitions provided in the EAC charter.

An independent echo core lab, composed of two experienced imaging cardiologists, assesses all baseline and follow-up TTE’s. Based on the baseline and 1-year follow-up LVEF, as assessed by the echo core lab, the echocardiographic part of the primary endpoint is determined. The echo core lab is blinded for the study number and date of the examination. Due to the presence of pacing leads, the core lab cannot be completely blinded to the allocation of the patient.

An ECG core lab, consisting of two experienced LBBAP implanters, assesses all paced baseline and 1-year follow-up ECG’s to determine the presence of RVP, deep septal pacing, or LBBAP according to the previously published definition.^9^ Capture of the left-sided Purkinje system is determined according to the current consensus.^9^

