### Statistical analyses of the secondary endpoint

For the secondary endpoints, the treatment groups will be compared using Cox proportional hazards regression, again adjusted for the stratification variables used in the randomization procedure. The secondary endpoints are analysed without corrections for multiplicity. Hazard ratios will be presented with associated 95% confidence interval. The proportional hazards assumption will be tested as the association between the scaled Schoenfeld residuals and follow-up time. Change in LVEF will be compared between groups using multivariable linear regression analysis. We will use multivariable generalized linear regression analysis with a link-function dependent on the specific distribution to assess between-group differences in diastolic function.

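### Minor: the primary logistic model uses baseline LVEF only as a split at 50%, so a little precision from a value that defines the echo endpoint goes unused

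*Protocol article*

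**What the plan says.** All references are to the Protocol article.

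- *Statistical analyses of the primary endpoint*: the analysis is "performed using logistic regression analysis, adjusted for sex, and LVEF category, as these were stratification variables for randomization". The only sensitivity analysis named there is complete case.
- *Randomization, blinding, and treatment allocation* defines the category: "Randomization will be stratified by sex and percentage of LVEF (i.e. LVEF <50% and LVEF ≥50" percent.
- *Primary endpoint*: the third component is "a more than 10%-point decrease in LVEF leading to an LVEF below 50%, which as a binary combined endpoint will be determined at 1-year follow-up".
- *Adjudication of endpoints*: "Based on the baseline and 1-year follow-up LVEF, as assessed by the echo core lab, the echocardiographic part of the primary endpoint is determined".
- *Patient population* sets the lower end of the range: "a left ventricular ejection fraction (LVEF) ≥ 40" percent.
- *Limitations* expects the echo part to supply about half or more of the primary endpoint.
- *Statistical analyses of the secondary endpoint*: "Change in LVEF will be compared between groups using multivariable linear regression analysis". No covariates are listed for this model. The phrase "again adjusted for the stratification variables used in the randomization procedure" belongs to the sentence on Cox regression.

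**The concern.** The primary model treats every patient with a baseline of 50% or more as having the same prognosis, apart from sex and treatment. The endpoint definition does not. A patient who starts at 52 and one who starts at 70 need different falls to become an echo event, and their risks can differ accordingly. The value that carries this information is read by the core lab and is already needed to score the endpoint, so using it in the model requires no new data. At stake is the width of the confidence interval and the power of the primary test, not the validity of either.

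**Working it through.** **The plan's own figure.** Inputs from *Sample size calculation*: 25% v 14%, power 80%, 5% level (two-sided assumed). With mean proportion 0.195,

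n = [1.96·√(2·0.195·0.805) + 0.8416·√(0.25·0.75 + 0.14·0.86)]² / 0.11² = (1.0982 + 0.4670)² / 0.0121 = 202.5, so 203 per group.

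This matches the article. The formula is unadjusted, so the sample size does not depend on the covariates chosen.

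**The fall that counts as an event.** For baseline b, the follow-up value must lie below both b − 10 and 50, so the fall must exceed max(10, b − 50).

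- b = 45, 52 or 60: more than 10 points.
- b = 65: more than 15 points.
- b = 70: more than 20 points.

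The requirement bends at 60, inside the upper category. A cut at 50 cannot represent it.

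**Effect on the primary test.** The article gives no LVEF distribution, so the following are assumptions: baseline normal and truncated at 40, with mean 57 to 62 and SD 7 to 9; follow-up LVEF linear in baseline with slope 0.2 to 1.0; residual SD 5 to 7; echo share 50 to 90%. Arm rates were calibrated to 25% and 14%. Each scenario had 1,500 simulated trials of 406 patients. The comparison was sex plus category against sex plus a linear spline with knots at 50 and 60. The rows below have SD 7 and clinical events unrelated to baseline LVEF.

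| Slope | Mean | Residual SD | Echo share | RVP risk at baseline 50–55 / 55–60 / 60–65 / 65+ | Power, category | Power, spline | Gain (points) |
|---|---|---|---|---|---|---|---|
| 0.2 | 60 | 7 | 75% | 15 / 27 / 32 / 27% | 80.0% | 80.3% | 0.3 |
| 0.4 | 57 | 7 | 50% | 21 / 29 / 31 / 24% | 78.9% | 79.3% | 0.4 |
| 0.7 | 60 | 7 | 50% | 26 / 30 / 27 / 18% | 81.1% | 80.8% | −0.3 |
| 0.9 | 60 | 5 | 75% | 32 / 35 / 25 / 9% | 79.7% | 81.9% | 2.2 |
| 1.0 | 62 | 5 | 90% | 41 / 42 / 26 / 6% | 79.9% | 83.8% | 3.9 |

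Across all 20 scenarios the gain was −0.3 to 0.6 points at slopes 0.2 to 0.7 (14 scenarios), 1.5 to 2.4 at slope 0.9 (four), and 3.4 to 3.9 at slope 1.0 (two). The Monte Carlo standard error of each power is √(0.8·0.2/1500), or about 1 point, so the gains at the lower slopes cannot be told from zero. A separate run of 4,000 trials (mean 58, SD 7) gave 78.1% with the category and 78.8% with a spline. Rejection under no effect was 4.6 to 4.9% whichever model was used.

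Risk is not monotone in baseline LVEF, and its peak moves with the slope. A single linear term would therefore recover only part of the information.

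**Shift in the estimate.** The unadjusted log odds ratio is ln[(0.14/0.86)/(0.25/0.75)] = −0.72. The category model averaged −0.72 to −0.74. The spline model averaged −0.74 to −0.76 at slopes up to 0.7, −0.76 to −0.79 at 0.9, and −0.81 to −0.83 at 1.0. This is non-collapsibility of the odds ratio, not removal of a bias. In two scenarios the averaged spline coefficient was unusable, which points to failed fits where few patients lie below 50%.

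**LVEF change.** If follow-up LVEF has slope β on baseline and residual variance σ², and V is the baseline variance within categories, then adding continuous baseline to a category-only model multiplies the variance of the treatment effect by σ² / [σ² + (1 − β)²·V]. For mean 60, SD 7, truncated at 40, V is 34.6.

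- β = 0.2, σ = 7: 49/(49 + 22.1) = 0.69.
- β = 0.4, σ = 7: 49/(49 + 12.5) = 0.80.
- β = 0.7, σ = 7: 49/(49 + 3.1) = 0.94.
- β = 0.9, σ = 5: 25/(25 + 0.3) = 0.99.
- β = 1.0: 1.00.

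The simulated ratios agree. The two endpoints pull in opposite directions: close tracking favours the primary analysis, and weak tracking favours the change analysis.

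**The case against.** The strongest reply is that the model adjusts for exactly the factors used to stratify and says so. That is sound practice, and the likely gain is within simulation error. This stands, and it is why the point is minor. It does not remove the point, because the article fixes the covariates of the primary model rather than leaving them open, and the better form costs nothing.

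Three stronger readings are tempting, and the document supports none of them.

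- *The primary estimate is biased by imbalance in baseline LVEF within the upper category.* Under randomisation, such imbalance is random error that the confidence interval already covers.
- *The LVEF-change analysis discards baseline LVEF or is distorted by regression to the mean.* The article calls that model multivariable and lists no covariates, so baseline LVEF is neither promised nor excluded. A condensed article may leave this to the full protocol or analysis plan. Regression to the mean acts equally on both arms in expectation.
- *The stated power fails.* It comes from an unadjusted formula and reproduces exactly.

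Nor does the split at 50% by itself call for further covariates such as age, or for a different effect measure.

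**Conclusion.** The point holds as a minor efficiency improvement to the primary model. Baseline LVEF enters only through the split at 50%, although the endpoint's own definition makes the required fall grow above 60, for a component expected to provide about half or more of the events. The planned analysis is valid without the change. The power gain is usually about 1 point or less, and up to about 4 points if follow-up LVEF tracks baseline very closely and echo events dominate. The simulated spline replaced the category and was piecewise linear. The form recommended under the fix was not itself simulated, but should behave similarly. For LVEF change there is only something to confirm, worth a variance reduction of about 0 to 30% over a category-only model. All these sizes rest on assumed LVEF distributions.

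**What to change.** Before unblinding, state that the primary logistic model keeps sex and LVEF category as used at randomisation and adds core-lab baseline LVEF as a restricted cubic spline. Fix three or four knots at quantiles of the pooled baseline values, chosen without reference to arm. Name the planned model as the fallback if the fit does not converge, since the group below 50% may be small. Carry the same baseline term in the imputation model, and note that the conditional odds ratio will be slightly further from 1 than under the category-only model. If the sponsor prefers to leave the published primary model alone, the spline version can be a pre-specified sensitivity analysis.

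For LVEF change, confirm in the analysis plan that continuous baseline LVEF is a covariate alongside the stratification factors.

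The cost is a few sentences and a dated record of the departure from the published model. There are no new data, no added visits and no change to the sample size.

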## Analyses

### Sample size calculation

Based on previously reported mortality, heart failure hospitalizations, and significant deterioration of LVEF,^2,6–8,22^ we estimate that the proportion of patients in the RVP group that will develop any of the composites of the primary endpoint before 1-year follow-up will be at least 25%. We expect an event rate of 14% for the LBBAP group. Event rates are based on the effect size of heart failure-related events by his pacing in those with ventricular pacing percentage >20%.^6^ When designing this trial, no data on event rates in LBBAP were available yet. The effect size of LBBAP was estimated to be equal to HBP when designing this trial. To achieve a power of 80% at the 5% level of significance, 203 patients per group, or 406 in total, would be needed. Accounting for around 15% loss to follow-up or patients not receiving the allocated intervention, 470 patients are needed.

After designing the trial, Sharma et al. reported an occurrence of the combined primary clinical endpoint of mortality, heart failure hospitalization, or upgrade to CRT among patients with ventricular pacing burden > 20%, in 26.1% in RVP and 8.4% in LBBAP after a mean follow-up of 1.5 years in a non-randomized trial (HR 0.32; 95% CI 0.19–0.54; *P* 0.001).^15^ This study included a longer follow-up duration but excluded the echocardiographic endpoint. The addition of the echocardiographic endpoint in the LEAP trial will generate more endpoints in a shorter follow-up duration. Therefore, the study by Sharma et al. is substantiating the sample size calculation.

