### Statistical analyses

Analyses will be executed on an intention-to-treat population. This population includes all patients who are randomized, regardless of the treatment they received. For example, all patients randomized to LBBAP and not receiving LBBAP (i.e. RVP or HBP) will be analysed according to their randomization group (thus LBBAP). The same counts for all patients randomized to RVP and not receiving RVP.

Given the possibilities of crossovers, as a secondary analysis, an exploratory per-protocol analysis will be performed to check for consistency and explore potential efficacy. The per-protocol analysis will include all patients randomized to LBBAP who received LBBAP and all patients randomized to RVP who received RVP.

The ECG corelab will assess all paced baseline and 1-year follow-up ECGs to determine the pacing type the patients are treated with. Descriptive statistics (i.e. count (%)) will be used to display the actual pacing types (i.e. RVP, LBBAP, or HBP) in both treatment groups.

Categorical baseline characteristics will be presented as count (percentage). Continuous characteristics will be presented as mean (± standard deviation) or median (interquartile range) as appropriate.

All primary and secondary study endpoints will be described in detail as count and percentage (binary endpoints), using Kaplan–Meier curves (time-to-first occurrence of an endpoint), Cox regression analysis, and as mean and standard deviation (continuous endpoint, i.e. LVEF), depending on the type of outcome. All null-hypothesis testing will be performed using a level of significance of α = 0.05.

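### Imputation is stated for echocardiographic data only: scoring of death and heart-failure hospitalisation after early loss is left open, and complete case analysis cannot test the missing-at-random assumption

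*Protocol article*

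**What the plan says.** The Primary endpoint section combines all-cause death, heart-failure hospitalisation and an LVEF decline into one outcome, "which as a binary combined endpoint will be determined at 1-year follow-up". Statistical analyses defines the intention-to-treat population: "This population includes all patients who are randomized, regardless of the treatment they received". The primary analysis "will be performed using logistic regression analysis, adjusted for sex, and LVEF category". The Limitations section adds that the echo component rules out a time-to-event analysis of the primary endpoint, so there is no censoring.

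On missing data, Statistical analyses of the primary endpoint makes three statements. One names what is imputed and how: "Missing echocardiographic data will be imputed using multiple imputation with fully conditional specification". Another settles how many completed datasets are drawn: "The amount of imputations will be set to the percentage of incomplete records". The last names the check on the result: "A complete case analysis will be used as a sensitivity analysis". No other missing-data sensitivity analysis is named.

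Loss is expected. The sample size section inflates the total to 470, "Accounting for around 15% loss to follow-up or patients not receiving the allocated intervention", without giving loss separately. The follow-up section schedules clinic visits at 6 and 12 months that record deaths and hospitalisations, and a further check of events once the last patient reaches 1 year.

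**The concern.** A patient who leaves the trial at month 4 lacks the 1-year echocardiogram and also eight months of observation for death and heart-failure hospitalisation. A logistic model on a binary outcome still needs a value for that patient. The stated imputation supplies an LVEF and nothing else. If the clinical components are then built from recorded events alone, the unseen months become event-free by default. That lowers the event rate in each arm, and lowers it more in the arm with more loss.

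The second part concerns the imputed echoes. Multiple imputation as described assumes missing at random. Complete case analysis leaves the same patients out and also treats their missingness as ignorable. Neither analysis varies the unseen outcomes, so agreement between them does not show that the result withstands informative missingness. This matters here because patients and treating teams know the allocation, the echo component rests on a single follow-up echocardiogram, and the Limitations section expects it to supply about half or more of the primary events.

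**Working it through.** **1. The plan's own figure.** Inputs from Sample size calculation: 25% in the RVP arm ("before 1-year follow-up will be at least 25" per cent), 14% in the LBBAP arm, 80% power, 5% significance (taken as two-sided), 1:1 allocation. The pooled rate is 0.195.

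n = [1.960·√(2·0.195·0.805) + 0.842·√(0.25·0.75 + 0.14·0.86)]² / 0.11² = (1.098 + 0.467)² / 0.0121 ≈ 202.5, so 203 per group. This matches exactly. With 470/2 = 235 per arm and no misscoring, power is 85.5%.

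**2. Literal scoring, equal loss.** Assumptions, because the article does not give them: a fraction L of each arm is lost; half of all events are clinical (the largest share consistent with the Limitations section); every clinical event in lost patients is missed (worst case); their echo is imputed at the full rate; extra variance from imputation is ignored. The observed rate is r − L·(r/2).

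| Loss in both arms | RVP | LBBAP | Power, 235 per arm |
|---|---|---|---|
| 0% | 25.0% | 14.0% | 85.5% |
| 5% | 24.4% | 13.7% | 84.4% |
| 10% | 23.8% | 13.3% | 83.3% |
| 15% | 23.1% | 13.0% | 82.0% |

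If echo supplies 70% of events instead of 50%, 15% loss leaves power at 83.5%.

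**3. Unequal loss, no true effect.** Both arms have a true rate of 25%, of which 12.5 points are clinical. The spurious difference is (L₂ − L₁)·12.5 points, in favour of the arm with more loss.

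| Loss | Spurious difference | Two-sided type I error |
|---|---|---|
| 5% vs 10% | 0.6 points | 5.3% |
| 5% vs 15% | 1.25 points | 6.2% |
| 0% vs 15% | 1.9 points | 7.6% |

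For 5% vs 15%: the standard error is √[(0.24375·0.75625 + 0.23125·0.76875)/235] = 0.0393, and the shift in z is 0.0125/0.0393 = 0.32.

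**4. Direction at the design rates.** With 10% loss in RVP and 5% in LBBAP: 25 − 0.10·12.5 = 23.75 and 14 − 0.05·7 = 13.65. The difference is 10.1 points instead of 11, which works against LBBAP. With 5% in RVP and 15% in LBBAP: 24.375 − 12.95 = 11.4 points, which works in its favour.

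**5. Departure from missing at random.** Assume that 10% of LBBAP patients have a missing outcome and that their true event rate exceeds the imputed rate by δ. For δ = 11 points, the true LBBAP rate is 14 + 0.10·11 = 15.1%, so the true difference is 9.9 points. For δ = 20 points, the rate is 16.0% and the difference 9.0 points. The stated analyses would show neither shift.

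**6. Number of imputations.** The Monte Carlo SD of z is about √(FMI/m), where FMI is the fraction of missing information. If FMI is close to the fraction incomplete, the stated rule gives, for 10% incomplete, √(0.10/10) = 0.10. One SD either side of z = 1.96 is 1.86 to 2.06, or p from 0.063 to 0.039. With m = 100 the SD is √(0.10/100) = 0.03.

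**The case against.** A reader might infer that the plan counts lost patients as free of death and heart-failure hospitalisation. The article does not say so. It is silent, and such patients could be treated as missing, be imputed on the composite, or have their status recovered. The end-of-study check may supply much of the missing information, and a missing echocardiogram does not by itself mean that clinical status is unknown. This part of the objection stands, so event-free scoring is only the literal consequence of the stated rule. Nothing in the article, however, says that the check reaches patients who have withdrawn or cannot be contacted.

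A reader might also infer that complete case analysis drops everyone who died before the 1-year echocardiogram. With assumed deaths of 5% and 3%, that would turn 25% vs 14% into (25 − 5)/0.95 = 21.1% vs (14 − 3)/0.97 = 11.3%. The endpoint definition does not support this: death is itself a primary event, so the outcome of a patient who died is known. The death rates are also not in the article.

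The article is condensed, and a full protocol or analysis plan may contain component rules and further sensitivity analyses. It therefore cannot be said that robustness will never be examined. The methods the article does fix, however, are imputation of echo data, complete case as the check, and a rule for the number of imputations, and these can be judged as stated.

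Finally, the effects are modest. Equal loss leaves power above 80% in every scenario shown, and more loss in RVP is conservative for the superiority claim. Monte Carlo noise matters only close to the threshold: at the design rates with 235 per arm, z is about 0.11/0.0366 = 3.0, where a shift of 0.10 changes nothing. All of this stands and limits the weight of the point.

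**Conclusion.** The point holds as a gap in the stated methods, and it is worth closing before unblinding. The stated imputation covers one component of a three-part binary outcome, and the scoring of the other two after early loss is open. If the literal reading were applied, the cost would be at most about 3.5 points of power under equal loss of up to 15%. Type I error would rise to about 6% under 5% versus 15% loss. The bias works against LBBAP if RVP loses more patients and in its favour if LBBAP does. These sizes rest on assumed loss rates, on half of events being clinical, and on every clinical event in lost patients being missed.

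The firmer part is the sensitivity analysis. Complete case cannot test missing at random, whatever the amount of loss. The number of imputations is a minor matter.

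**What to change.** 1. For patients lost without an event, and whose status the end-of-study check does not recover, impute the clinical component for the unobserved period together with 1-year LVEF, by arm. Keep any adjudicated death or heart-failure hospitalisation as an event.
2. Make a delta-adjusted tipping-point analysis by arm the main missing-data sensitivity analysis. Keep complete case as a supplement, defined on the composite.
3. Fix the number of imputations at a larger value, for example at least 100.

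If the full protocol or analysis plan already contains these rules, confirming that is enough. The cost is wording, extra analysis and computing time. Design and conduct do not change, and the 203 per group stays as it is.
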